#### Data Management

Study data are recorded in each patient’s medical notes before being recorded onto eCRFs, which are developed and managed by the NCTU. The eCRF has been built using the Red Pill system supplied by Sealed Envelope Ltd. Data entered onto the eCRF must be consistent with the information in the medical notes. Patients are identified using a unique study ID; all data passed to the NCTU will have patient identifiers removed, with the exception of date of birth, gender, ethnicity, and study ID. Data cleaning is provided by staff within the NCTU.

#### Statistical Analysis

Primary analysis will follow intention-to-treat principles with patient data analyzed according to randomization and irrespective of intervention received; other analysis groups, such as per-protocol groups, may be considered subsequently. Every effort will be made to retain and include all patients who are part of the trial.

Data will be summarized by study group. Mean or median will summarize continuous variables, whereas number and percentage will be used to summarize categorical variables. A general linear model will be used to analyze the primary outcome considering all covariates used in the randomization scheme. Similar methods will be used to analyze all continuous secondary outcomes. Data of other types will be analyzed using generalized linear models with appropriate distributions.

The numbers of MACCE after 12 months will be compared between arms by the use of standardized rates (eg, by consideration of the number of events per patient month in each arm). Impact of missing data will be explored by tabulating the proportion of missing data in each arm. A full statistical analysis plan will be developed for the outcome measures and agreed upon with the IDMEC and the chief investigator prior to any analysis being undertaken.

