**Methods:**

The study was designed as a single-center, randomized, double-blind, parallel-group, placebo-controlled phase II trial. Recruitment started in January 2019. A total of 90 patients, aged 65 years or older, with treated ACS who have had CHD confirmed by angiography will be enrolled. They will be randomized to one of two groups: TA-65MD oral therapy (8 mg twice daily) or placebo taken for 12 months. The primary outcome is the effect on immunosenescence determined by a decrease in the proportion of CD8+ TEMRA (T effector memory cells re-expressing CD45RA [CD45 expressing exon A]) cells at 12 months. Secondary outcomes include leukocyte telomere length, endothelial function, cardiac function as measured by echocardiography and NT-proBNP (N-terminal fragment of the prohormone brain-type natriuretic peptide), systemic inflammation, oxidative stress, and telomerase activity.

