**Interventions**								
	Randomization—stratified	X						
	Dispensing of investigational medicinal product (IMP)		X	X	X	X	X	X
	Return of unused IMP and drug adherence			X	X	X	X	X
	Adverse events evaluation			X	X	X	X	X

^a^Baseline assessments are completed after written consent is obtained and are performed before randomization.

^b^IgG: immunoglobulin G.

^c^TEMRA: T effector memory cells re-expressing CD45RA (CD45 expressing exon A).

^d^Results from baseline immunosenescence sample are required for randomization.

^e^hsCRP: high‐sensitivity C‐reactive protein.

^f^NT-proBNP: N-terminal fragment of the prohormone brain-type natriuretic peptide.

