### Primary Outcome

The primary outcome is immunosenescence following 12 months of treatment with TA-65MD. Immunosenescence will be determined by flow cytometry and fluorescence-activated cell sorting (FACS) (see Figure 1); the proportion of terminally differentiated CD8+ effector memory cells (% CD8+ TEMRA [T effector memory cells re-expressing CD45RA (CD45 expressing exon A)]) will be calculated from the total number of peripheral blood CD8+ T lymphocytes. We have previously demonstrated the prognostic utility of CD8+ TEMRA as a measure for immunosenescence [19]. The mean difference between the intervention and control arms will be compared at 12 months.

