#### Randomization

Randomization will be performed using the Sealed Envelope Ltd system with a minimization scheme to ensure patients randomized to each group are comparable at baseline. The minimization scheme will account for (1) gender (male or female), (2) type of ACS (ST elevation myocardial infarction [STEMI] or non-ST elevation myocardial infarction [NSTEMI]), and (3) CD8+ TEMRA (high >45% or low ≤45%) at baseline.

Eligible patients will be randomized by delegated and trained members of the research team at each center using the 24-hour, central, secure, web-based randomization system with concealed allocation. Eligible patients will be randomized in a 1:1 ratio to receive TA-65MD (intervention under study) or placebo (control arm).

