### Statistical Considerations

#### Overview

A pragmatic decision was taken to recruit and analyze data on 90 patients: 45 in each group. This sample size is the minimum conventional threshold for making parameter estimates in pilot studies [33]. The parameter estimates in this trial will be used to inform a large, multicenter clinical trial. 

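### As worded, the primary model adjusts for baseline CD8+ TEMRA only as a high/low split at 45%; the comparison stays valid but gives up precision that the measured percentage would supply at no cost

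*Protocol article*

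**What the plan says.** The Statistical Analysis section states: "A general linear model will be used to analyze the primary outcome considering all covariates used in the randomization scheme". The Randomization section lists three minimization factors: gender, type of ACS (STEMI or NSTEMI), and "CD8+ TEMRA (high >45% or low ≤45%) at baseline". Nowhere does the article add the baseline percentage as a continuous covariate.

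Footnote d to Table 1 says: "Results from baseline immunosenescence sample are required for randomization". Every randomized patient should therefore have a measured baseline value.

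The Primary Outcome section defines the outcome on a continuous scale, as a proportion that "will be calculated from the total number of peripheral blood CD8+ T lymphocytes", and sets the contrast: "The mean difference between the intervention and control arms will be compared at 12 months". The abstract words the same outcome differently, as immunosenescence "determined by a decrease in the proportion of CD8+ TEMRA" cells at 12 months.

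On size, the Overview under Statistical Considerations says: "A pragmatic decision was taken to recruit and analyze data on 90 patients: 45 in each group". It presents this as a pilot convention and says the estimates are meant to inform a larger trial. A full SAP is to be agreed before any analysis; it is not shown.

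**The concern.** For a continuous outcome measured at baseline and again at follow-up, the baseline value is often the strongest predictor available. Cutting it at 45% treats a patient at 46% and a patient at 80% as equal, and separates patients at 45% and 46%. Differences between patients within each half, including any chance imbalance between arms there, stay in the error term.

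At stake is the width of the confidence interval for the primary comparison. That matters here because the 90 patients are justified by the parameter estimates they will yield.

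There is a second, smaller consequence. The abstract can be read as describing change from baseline, while the Primary Outcome section compares 12-month values. With only the split in the model, those two analyses give different treatment estimates in the same data.

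**Working it through.** **The plan's own figure.** 45 + 45 = 90 agrees. No alpha, power, effect size or SD is given, so there is no power calculation to reproduce.

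**Inputs from the article.** Continuous outcome compared at 12 months (Primary Outcome); three minimization factors with TEMRA cut at 45% (Randomization); baseline result in hand before randomization (Table 1, footnote d); 1:1 allocation.

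**Assumed, because the article does not give them.** The correlation r between baseline and 12-month TEMRA (0.3 to 0.9); the share p of patients above 45% (50%, then 30% and 20%); bivariate normality; for the change score, equal variance at both times. Outcome variance is set to 1, and all patients are taken as analysed.

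**Step 1: what the split keeps.** A normal covariate cut at c, with share p above the cut, keeps the fraction k = φ(c)² / [p(1 − p)] of the variance that the full covariate explains. At p = 50%, k = 0.3989² / 0.25 = 0.637 (that is, 2/π). At p = 30%, k = 0.576; at p = 20%, k = 0.490.

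**Step 2: 12-month value as outcome.** Residual variance is 1 − r² with the continuous baseline and 1 − k·r² with the split. Their ratio is the variance ratio for the treatment effect, and its square root is the ratio of confidence interval widths. At p = 50%:

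| r | Continuous | Split | Variance ratio | CI wider by | 90 patients with split equal this many with continuous |
|---|---|---|---|---|---|
| 0.3 | 0.910 | 0.943 | 1.04 | 2% | 87 |
| 0.5 | 0.750 | 0.841 | 1.12 | 6% | 80 |
| 0.7 | 0.510 | 0.688 | 1.35 | 16% | 67 |
| 0.8 | 0.360 | 0.593 | 1.65 | 28% | 55 |
| 0.9 | 0.190 | 0.484 | 2.55 | 60% | 35 |

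A simulation of 90 patients (4000 runs, allocation balanced on the split) gave variance ratios of 1.11, 1.36, 1.68 and 2.58 at r = 0.5, 0.7, 0.8 and 0.9, in line with the formula.

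**Step 3: uneven split.** At r = 0.3, 0.5, 0.7, 0.8 and 0.9 the variance ratios are 1.04, 1.14, 1.41, 1.75 and 2.81 with 30% above the cut, and 1.05, 1.17, 1.49, 1.91 and 3.17 with 20% above it.

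**Step 4: change score as outcome.** With a median split, the residual variance is 2(1 − r) − 0.637(1 − r)². At r = 0.7 this is 0.600 − 0.057 = 0.543, and 0.543 / 0.510 = 1.06. The ratios at r = 0.5, 0.7, 0.8 and 0.9 are about 1.12, 1.06, 1.04 and 1.02 (CI about 6%, 3%, 2% and 1% wider). At r = 0.3 the change score does worse: (1.400 − 0.312) / 0.910 = 1.20.

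**Step 5: why the continuous baseline reconciles the two framings.** Write the 12-month model as Y = a + τT + βX + other terms, with X the baseline percentage. Subtracting X from both sides gives Y − X = a + τT + (β − 1)X + other terms. Only the slope on X changes; τ and its standard error do not. If X enters only as a split, the change-score estimate equals the 12-month estimate minus the adjusted difference between arms in baseline TEMRA. The two agree only when that difference happens to be zero.

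**The case against.** The strongest reply concerns the wording. The sentence requires the randomization covariates to be considered. It does not say that only those are allowed, or in what form they enter. The 45% cut is defined as a minimization level, and a SAP that enters the percentage itself would be compatible with the article. This stands in part: the binary reading is the natural one, not an explicit statement. It does not remove the point, because the article names a covariate set, and following it as written leads to the split.

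The size is also open to challenge. The large figures need a correlation of 0.7 or more and the 12-month value as outcome. At lower correlations, or with a change score at high correlation, the loss is small. This stands, which is why both framings and the lower correlations are shown. The Primary Outcome section favours the 12-month comparison.

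Three stronger readings are tempting and not supported:

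- A reader might infer that the estimate is biased or the test invalid. It is not. Adjusting for minimization factors is sound, and chance imbalance within the strata adds variance, not systematic error.
- A reader might infer that 45 per arm is too few. The article sets no power or precision target, so no target is missed.
- A reader might infer that an inflated variance must pass into the larger trial's sample size. That does not follow: the SD and the baseline correlation can be estimated from the stored continuous values, whatever the primary model.

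**Conclusion.** The point holds as a loss of efficiency. As worded, the plan adjusts a continuous outcome for a dichotomy of its own baseline although the exact value is in hand.

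For the 12-month comparison, under normality and a median split, the cost runs from negligible (about 2% on the interval width at a correlation of 0.3) to large (about 60% at 0.9), and it is greater if the split is uneven. Under a change-score reading it is about 6% at 0.5 and falls to about 1% at 0.9. The article does not give the correlation or the share above 45%, so no single figure can be claimed. The direction is the same for any non-zero correlation in the 12-month comparison.

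This is a recommended improvement, not a flaw that must be repaired before the trial can be interpreted.

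**What to change.** Before any analysis, state the primary model as an ANCOVA of 12-month %CD8+ TEMRA on treatment, continuous baseline %CD8+ TEMRA, gender and ACS type. The high/low minimization factor may stay in as well. Say in the same place that the 12-month and change-score versions give the same treatment effect under this model, so that the abstract and the Primary Outcome section describe one analysis.

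The cost is one sentence in the statistical section and the SAP. No new data, visits or patients are needed. If the unseen SAP already enters the baseline percentage as a continuous term, it is enough to align the article's sentence with it.

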**Assessments**								
	Blood pressure	X		X	X	X	X	X
	Capillary glucose	X		X	X	X	X	X
	Physical assessment of height and weight	X						
	Venous sample (5 mL) cytomegalovirus IgG^b^	X						
	Venous sample (4 mL) CD8 TEMRA^c^ immunosenescence (primary outcome)^d^	X				X		X
	Venous sample (36 mL) CD8 and CD4 immunosenescence (secondary outcomes), telomere length, and telomerase activity	X				X		X
	Venous sample (4 mL) oxidative stress, future use	X				X		X
	Venous sample (5 mL) future research use—optional consent	X				X		X
	Venous sample (5mL) hsCRP^e^ and NT-proBNP^f^	X				X		X
	Endothelial function (EndoPAT [Peripheral Arterial Tone])	X				X		X
	Echocardiography	X						X

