### Inclusion and Exclusion Criteria

Textbox 1 lists the criteria informing the eligibility or exclusion of patients for the trial.

Inclusion and exclusion criteria.Inclusion criteria—patients will be eligible for the trial if they:Provide written informed consentAre male or female, aged 65 years or over, with an index presentation of an acute coronary syndrome (ACS)* within the previous 6 monthsHave successfully completed revascularization** or are being managed medically following ACSHave angiographic evidence of coronary heart disease: at least one major epicardial vessel stenosis ≥70%Are recruited more than 24 hours after presentation with the index ACS event*ACS defined as either a non-ST elevation myocardial infarction (NSTEMI) or ST elevation myocardial infarction (STEMI)**Percutaneous coronary intervention or angioplasty, eligible the following day, or coronary artery bypass grafting, eligible 3 months following surgeryExclusion criteria—patients will be excluded from the trial if they:Have any disorder associated with immunological dysfunction (ie, acute or chronic inflammatory or neoplastic coexisting disease, known positive serology for HIV, or hepatitis)Are clinically unstable (ie, hemodynamically unstable, cardiogenic shock, or unconscious)Have severe, uncontrolled hypertension (blood pressure [BP] >170/110 mmHg or ambulatory BP of 150/95 mmHg)Have a severe comorbidity that has impact on outcome over the next 2 yearsAre taking immunosuppressantsHave a known malignancyCurrently use a nutritional supplement derived from the roots of theAstragalusspeciesHave a previous known substance addictionHave insulin-dependent diabetesAre judged by the investigator that they should not participate in the study, for example, on the basis of previous serious psychiatric illness or are unlikely to comply with study procedures, restrictions, and requirementsHave participated in any other interventional medicinal study in the past 6 months

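### The covariates named for the continuous secondary outcomes leave out each outcome's own measured baseline, which costs precision but not validity

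*Protocol article*

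**What the plan says.** Under Statistical Analysis, the article sets the primary model: "A general linear model will be used to analyze the primary outcome considering all covariates used in the randomization scheme". It continues: "Similar methods will be used to analyze all continuous secondary outcomes".

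The section on Randomization lists the covariates: gender, type of ACS (STEMI or NSTEMI), and "CD8+ TEMRA (high >45% or low ≤45%) at baseline".

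Table 1 schedules a baseline measurement for every laboratory or imaging secondary outcome. One example is the row "Venous sample (5mL) hsCRP^e^ and NT-proBNP^f", marked at baseline, 6 and 12 months. Telomere length, telomerase activity, oxidative stress and EndoPAT follow the same schedule; echocardiography is done at baseline and 12 months. No sentence names any of these baselines as a model term.

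The same section promises a full statistical analysis plan before any analysis. That plan is not shown.

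**The concern.** For the primary outcome, the TEMRA category is a coarse version of the outcome's own baseline, so the named covariates do part of the work. When they are carried over to telomere length or reactive hyperemic index, the TEMRA category is the baseline of something else. Between-patient variation that the trial has already measured at baseline then stays in the residual.

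This fits the telomere hypothesis poorly. The Trial Rationale and the section on CD8 T Cell Telomere Length speak of less shortening over the year, which is a statement about where each patient started.

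The stakes are set by the article itself. The Abstract's Conclusions and the Discussion make a larger trial depend on improved telomere length and endothelial function as well as on fewer senescent CD8+ cells. The Overview under Statistical Considerations says that the parameter estimates will inform that trial. The sample size is a pragmatic 45 per arm, with no power calculation, so avoidable width in these intervals weakens the stated purpose.

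**Working it through.** **Plan's own figure.** There is none to reproduce. The article gives no alpha, power, SD, baseline correlation or target difference for any secondary outcome.

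**Inputs.**
- n = 45 per arm, 1:1 (Trial Design; Overview under Statistical Considerations).
- r, the correlation between an outcome's baseline and its 12-month value within arm and given the minimization factors: assumed, range 0.3 to 0.8.
- Two-sided 5% level: assumed.
- For the power column, a true difference of 0.5 SD: assumed, for illustration.
- Full follow-up: assumed. Missing 12-month values would widen both intervals.

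**Interval without the own baseline**, in units of the outcome's residual SD:

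1.96 × √(2/45) = 1.96 × 0.211 = 0.413.

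**Interval with the own baseline.** The residual variance is multiplied by 1 − r², so the half-width is 0.413 × √(1 − r²). The one degree of freedom spent is negligible at 90 patients. Power is Φ[0.5 / (0.211 × √(1 − r²)) − 1.96].

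| Assumed r | √(1 − r²) | 95% CI half-width (SD) | CI narrower by | Equivalent n per arm, 45/(1 − r²) | Power for 0.5 SD |
|---|---|---|---|---|---|
| no baseline term | 1.00 | 0.41 | – | 45 | 66% |
| 0.3 | 0.95 | 0.39 | 5% | 49 | 70% |
| 0.5 | 0.87 | 0.36 | 13% | 60 | 78% |
| 0.6 | 0.80 | 0.33 | 20% | 70 | 84% |
| 0.7 | 0.71 | 0.30 | 29% | 88 | 91% |
| 0.8 | 0.60 | 0.25 | 40% | 125 | 98% |

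**Validity.** A chance baseline difference of δ SD moves the unadjusted 12-month contrast by r × δ. With 45 per arm, the standard error of the baseline difference is 0.211 SD. At r = 0.7, an imbalance of one standard error therefore shifts the contrast by 0.7 × 0.211 = 0.15 SD. Over repeated randomizations these shifts average to zero and are already counted in the unadjusted standard error.

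A simulation agrees. It used a lognormal marker with log-SD 0.5, 1.0 or 1.2, baseline correlation 0.5 or 0.7, and 2,000 runs per setting with no treatment effect. Linear models without the own baseline rejected in 3.2% to 5.6% of runs, whether fitted to raw or logged values.

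**The case against.** The strongest reply is that a journal article condenses the plan, says similar rather than identical methods, does not say that only the minimization factors enter, and defers detail to the analysis plan. Since the primary model contains a categorized version of its own baseline, a similar model could be taken to use each secondary outcome's own baseline.

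Part of this stands: the article does not exclude the own baseline, and the analysis plan may include it. But the article does more than stay silent. It names a covariate set and extends the method to all continuous secondary outcomes. Read as written, that set lacks the most useful covariate, and a promise of further detail does not by itself correct it.

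A reader might infer four stronger points, which the article does not support:

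- **That all secondary outcomes will be analysed on the raw scale.** No scale is stated, and a linear model can be fitted to logged values. The sentence "The mean difference between the intervention and control arms will be compared at 12 months" concerns the primary outcome only. "Mean or median will summarize continuous variables" shows that skewed variables were foreseen, at least for description.
- **That a few patients will drive the comparison of hsCRP or NT-proBNP.** The article gives no distribution for either, so this depends wholly on assumed skew. In the simulation, with a true ratio of 0.6, power without the own baseline was 46–48% raw against 64–67% logged at log-SD 1.0. At log-SD 0.5 it was 99% or more on either scale. Neither marker is among the stated conditions for a larger trial.
- **That baseline imbalance biases the contrasts.** It adds noise, as shown above.
- **That time since the index ACS must be a covariate**, because entry runs from 24 hours ("Are recruited more than 24 hours after presentation with the index ACS event") to 6 months after the event. That is a preference; no figure in the article shows what it would gain. If timing does add spread to baseline hsCRP and NT-proBNP, it would probably lower their correlation with 12 months and shrink the gain from baseline adjustment.

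**Conclusion.** The point holds for the covariate set and for precision only. As named, the models for the continuous secondary outcomes adjust for gender, ACS type and TEMRA category but not for the outcome's own baseline, which the trial collects.

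The direction of the gain is certain wherever baseline and 12-month values are materially correlated. Its size rests on assumed correlations: 13% to 40% off the interval width for r from 0.5 to 0.8, and about 5% at r = 0.3. The power figures rest in addition on the assumed 0.5 SD difference. It matters most for telomere length and reactive hyperemic index, because of their place in the decision on a larger trial.

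No invalid test and no biased estimate follows from the plan as written. The choice of scale for hsCRP and NT-proBNP remains open and is not an error.

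**What to change.** In the analysis plan, state that the model for every continuous secondary outcome contains treatment, the minimization factors and that outcome's own baseline as a continuous variable, on the same scale as the outcome. Settle telomere length and reactive hyperemic index first. If the analysis plan already says this, nothing more is needed.

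As advice only, the analysis plan should also fix the scale for hsCRP and NT-proBNP before unblinding. If they are logged, the treatment effects are reported as ratios of geometric means.

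The cost is wording before analysis and one degree of freedom per model. No new data, visits or samples are needed. For an outcome kept on its present scale, the quantity estimated is still the difference between arms at 12 months.
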